## Abstract

**Abstract:**

**Background:**

Respiratory viral infections (RVIs) are a significant cause of morbidity and hospital admission worldwide. However, the management of most viral infection-associated diseases remains primarily supportive. The recent COVID-19 pandemic has underscored the urgent need for a deeper understanding of RVIs to improve patient outcomes and develop effective treatment strategies. The Understanding Infection, Viral Exacerbation and Respiratory Symptoms at Admission-Longitudinal Study is an observational study which addresses this need by investigating the heterogeneity of RVIs in hospitalised adults, aiming to identify clinical and biological predictors of adverse outcomes. This study aims to bridge critical knowledge gaps in the clinical course and the economic impact of RVIs by characterising the phenotypic diversity of these infections and their recovery patterns following hospital admission and thus assisting with the optimal design of future interventional studies.

**Methods and analysis:**

This prospective longitudinal observational study (V.6, 20 September 2023) will be conducted across multiple UK secondary care sites from August 2022 onwards, with an aim to enrol 1000 participants testing positive for RVI. Adults admitted with respiratory symptoms who test positive for RVIs via the BioFire® FilmArray® System or other validated diagnostic PCR tests will be enrolled. The data collected include patient demographics, clinical history, comorbidities and symptoms experienced prior to, during and after hospitalisation with follow-up after discharge at weeks 1, 2, 4, 8, 12 and 26. In addition, biological samples are collected at multiple time points during the hospital stay. The primary endpoints are to study the impact of different RVIs and identify predictors of disease progression and length of stay. Secondary endpoints include time to recovery and healthcare cost. Exploratory endpoints focus on biomarker profiles associated with virus type and clinical outcomes.

**Ethics and dissemination:**

The study protocol received ethical approval from the relevant committees (English Ethics Reference Number: 22/WM/0119; Scottish Ethics Reference Number: 22-SS-0101, 20/09/2023). For patients who lack the capacity to consent, the study complies with the Mental Capacity Act 2005, using a consultee process where a family member, carer or an independent clinician may provide assent on behalf of the patient. Data from all the study centres will be analysed together and disseminated through peer-reviewed journals, conference presentations and workshops. The study group will ensure that participants and their families are informed of the study findings promptly and in an accessible format.

**Trial registration number:**

ISRCTN49183956.

Strengths and limitations of this studyMulticentre design, a diverse representative UK population sample, enhances generalisability.Comprehensive data collection at multiple time points allows for detailed analysis of disease progression and recovery.Establishment of a biorepository will facilitate future research on respiratory viral infections.Enhance optimal design of future interventional studies.Reliance on UK hospital-based recruitment may limit generalisability to non-hospitalised populations and non-UK populations.

## Introduction

### Background

 Respiratory viral infections (RVIs), such as influenza, respiratory syncytial virus (RSV) and SARS-CoV-2, are frequently associated with hospital admission, particularly among vulnerable populations such as elderly individuals and those with chronic health conditions.^1^ Despite their prevalence and impact, there is a lack of detailed understanding regarding the clinical course, phenotypic variability and long-term outcomes of the wider spectrum of RVIs. Previous studies have often focused on single viral pathogens or specific patient populations, often neglecting the broader spectrum of respiratory viruses and their diverse clinical presentations.^2^
^3 4^

The recent COVID-19 pandemic has underscored the need for research that links clinical care with rapid translation of new treatment discoveries.^5^ Understanding the natural history of acute RVIs and recovery will facilitate improved clinical management and potentially identify intervention options for those at risk of severe disease, resulting in health economic benefits.

The Understanding Infection, Viral Exacerbation and Respiratory Symptoms at Admission-Longitudinal (UNIVERSAL) observational study aims to address these critical knowledge gaps by providing a comprehensive analysis of RVIs in a diverse cohort of hospitalised adults in the UK. By capturing detailed clinical, biological and economic data across multiple time points, this study seeks to enhance our understanding of the natural history of these infections, identify biomarkers for disease severity and recovery and allow optimal design of future interventional studies.

### Objectives of the UNIVERSAL study

#### Primary objectives

Develop phenotypic characterisation of the heterogeneous nature of acute RVI and recovery seen in patients admitted to hospital with respiratory symptoms.

#### Secondary objectives

Enable accurate stratification of patients for the optimal design of future studies on novel pharmacological and non-pharmacological treatment strategies.Establish a biorepository of biological samples to facilitate endotype-level understanding of disease clusters.Develop an understanding of healthcare cost estimates for each patient.

#### Exploratory objectives

Explore immune and inflammatory biomarkers associated with virus type, disease severity, recovery and length of stay to enable a precision medicine strategy.

## Methods and design

### Study design

The UNIVERSAL study is a multicentre, prospective, longitudinal, observational cohort study conducted across multiple secondary care hospitals in the UK. This multicentre approach allows the study to capture diverse patient demographics reflective of various geographic regions and healthcare settings across the UK. Participant enrolment began on 31 August 2022, with a target of 1000 RVI positive participants, and a planned end date of December 2025.

### Patient and public involvement

Patients and the public were involved in the design and planning of the UNIVERSAL study. The study team engaged with patient advocacy groups and individuals with lived experience with RVIs to ensure that the research addresses the issues most relevant to patients and their families. This involvement informed the selection of study outcomes, the development of patient information materials and the consent process and the design of the study protocol. This approach helped ensure that the data collection methods were patient-centred and minimally burdensome. This feedback helped shape the follow-up schedule of patient-reported outcome (PRO) measures.

A patient advisory group will meet with the research team during the study to review the study procedures. This group provides ongoing feedback on study materials and advises dissemination strategies to ensure that findings are communicated effectively to a lay audience. Findings from the study will be shared through accessible formats such as newsletters, public talks and social media updates, in addition to academic publications and conference presentations.

### Setting

The UNIVERSAL study is being conducted across 10 secondary care hospitals in the UK detailed in table 1. These hospitals were selected to provide a comprehensive representation of both urban and rural healthcare settings to try and enable a representative sample of the UK population. The participating hospitals are equipped with the necessary facilities and expertise to manage patients with acute RVIs, including advanced diagnostics and intensive care capabilities.

**Table 1 T1:** UNIVERSAL recruitment centres and their recruitment timelines since August 2022

UNIVERSAL recruitment centre	Date opened to recruitment	Date closed to recruitment
University Hospital Southampton	31-Aug-2022	Recruitment ongoing
Castlehill Hospital, Hull	07-Nov-2022	May 2024
Royal Devon and Exeter University Healthcare	14-Nov-2022	June 2023
Derriford Hospital, Plymouth	10-Nov-2022	Recruitment ongoing
Addenbrooke’s Hospital, Cambridge	07-Feb-2023	February 2024
Princess Royal Hospital, Haywards Heath	07-Feb-2023	Recruitment ongoing
Glenfield Hospital, Leicester	21-Feb-2023	November 2023
Queen Elizabeth Hospital, Birmingham	23-Aug-2023	Recruitment ongoing
Royal Sussex County Hospital, Brighton	18-Sep-2023	Recruitment ongoing
St Mary’s Hospital, London	02-Oct-2023	Recruitment ongoing
Ninewells Hospital Dundee	25-Mar-2024	Recruitment ongoing

The UNIVERSAL Study is currently recruiting across several UK centres to gather comprehensive data on the spectrum of respiratory viral infections (RVIs) in hospitalised adults, covering a wide geographic area.

UNIVERSAL, Understanding Infection, Viral Exacerbation and Respiratory Symptoms at Admission-Longitudinal.

#### Participating hospitals

Table 1 provides a list of UNIVERSAL study recruitment centres and the applicable dates of recruitment. Recruitment is currently ongoing at seven active sites. Further recruitment centres are planned to open in 2024 to ensure ongoing recruitment into 2025.

#### Recruitment period

Recruitment for the UNIVERSAL study began in August 2022 and will continue until 1000 RVI positive participants are recruited. The recruitment process involved identifying eligible patients who meet the inclusion criteria on admission to the participating hospitals with respiratory symptoms, figure 1. This study aims to enrol a total of 1000 RVI-positive patients, capturing a broad spectrum of RVIs. Participants who test negative for RVI have baseline clinical data collected, and as per protocol amendment V.6.0 on 20 September 2023, a subset of participants testing negative for RVI have samples collected to act as a control group.

**Figure 1 F1:**
[figure not shown]
UNIVERSAL study recruitment pathway. Potential participants are identified by research staff through detailed review of the clinical records to ensure that eligibility criteria are met. Each participant is then provided with information regarding the study, and a written informed consent form is obtained. *ARI includes acute respiratory symptoms that may be caused by conditions such as acute upper or lower respiratory tract infections or acute exacerbation of chronic respiratory diseases. **Participants who test negative for RVI have baseline clinical data collected, and as per protocol amendment V.6.0 on 20 September 2023, a subset of participants testing negative for RVI have samples collected to act as a comparison cohort. Created with BioRender.com. RVI, respiratory viral infection; UNIVERSAL, Understanding Infection, Viral Exacerbation and Respiratory Symptoms at Admission-Longitudinal.

### Participants

#### Eligibility criteria

Eligible participants for the UNIVERSAL study are identified on their admission to the hospital with respiratory symptoms. To qualify for the study, individuals must meet specific inclusion criteria at the time of screening. The eligibility criteria, recruitment process and participant pathway through the study are detailed in figure 1.

To be eligible, participants must be aged 18 years or older and exhibit features of an acute respiratory illness. This includes conditions such as acute upper or lower respiratory illnesses (eg, rhinitis, rhinosinusitis, pharyngitis, pneumonia, bronchitis and influenza-like illness) or an acute exacerbation of a chronic respiratory illness (such as chronic obstructive pulmonary disease (COPD), asthma or bronchiectasis). The diagnosis must be confirmed by a treating clinician. Additionally, participants must have been admitted as medical inpatients within the past 36 hours, with the admission time defined as the point at which the decision was made to admit the patient rather than the time of their arrival at the hospital.

Furthermore, participants must have a positive test result for RVI using the BioFire® FilmArray® System or other NHS Trust approved diagnostic PCR test during the current admission to be enrolled in the virus positive arm. A range of viral PCR platforms are employed by NHS Trusts in the UK which detect common respiratory viral pathogens including RSV, influenza and SARS-CoV-2. If on admission, a potential participant has tested negative using a limited respiratory virus PCR panel, once consented to UNIVERSAL, a respiratory tract swab sample is obtained and run on the BioFire® FilmArray® System to detect an extended panel of respiratory pathogens, including influenza A and B, RSV, SARS-CoV-2, parainfluenza viruses 1–4, human metapneumovirus, rhinovirus/enterovirus, adenovirus and coronaviruses 229E, NL63, OC43, HKU1. This ensures that a broad range of respiratory viral pathogens are included in the study. Participants who test negative for RVI have baseline data collected only. Participants are excluded from the study if they meet any of the following criteria: they or their consultee decline consent, they cannot undergo combined nasal and throat swabbing due to either personal refusal or a medical contraindication. Participants enrolled in the UNIVERSAL study who test positive for RVI, and complete study procedures cannot be enrolled a second time.

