### Sample collection and Biobanking

All UNIVERSAL participants consent to provide biological samples as part of the study procedures. Samples are taken on day 1, 3 and 7 of enrolment while participants remain in hospital as detailed in online supplemental material 2. The biological samples provided include blood, upper respiratory tract swabs and nasal lining fluid. After initial storage at individual recruitment centres, samples are transferred to a secure UK biobanking facility for longer-term storage. Biological samples are anonymised and can be linked to clinical data collected as part of the study using anonymised participant identification numbers. In line with study objectives, this provides a biorepository of clinical samples to allow the exploration of inflammatory biomarkers associated with virus type and disease severity.

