### Variables

#### Primary outcomes

The primary outcomes of the UNIVERSAL study are focused on characterising the clinical impact of RVIs in hospitalised adults. This includes not only documenting the occurrence of various respiratory viruses, including influenza, RSV and SARS-CoV-2, but also a broader range of viruses such as rhinoviruses, parainfluenza viruses and human metapneumovirus. The study aims to evaluate their association with disease severity, progression and recovery. The study also aims to identify clinical and biological predictors of these outcomes, including markers such as viral load, inflammatory markers such as C reactive protein (CRP) and patient demographics. Another key outcome is measuring the duration of hospital stay for patients with RVIs and understanding the factors that contribute to prolonged hospitalisation.

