### Sample size calculation

Based on previous studies and expected variability in outcomes, a sample size of 1000 patients is estimated to provide sufficient power to detect significant differences in primary outcomes for the most prevalent respiratory viruses.^9 10^ In terms of descriptive statistics on the incidence/prevalence rates, 1000/2000 participants would conservatively allow the estimation with a 95% CI of ±3.1%/2.2%. There is little consensus in the literature on how best to calculate a formal sample size for cluster analysis such as latent class modelling. Simulation studies have suggested that sample sizes in the order of 500–1000 participants are usually sufficient even in the presence of weak class-indicator associations for 80% power or greater.^9 10^ To develop a clinical prediction model of progression of illness, a minimum sample size of 932 would be required. This assumes that for a model to be useful, it would need to have an area under the receiver operating characteristic (ROC) curve of at least 0.85 and is based on an outcome prevalence of 10% and up to 18 parameters in the final model.

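### As written, the extended virus panel is triggered only by a negative limited panel, so whether the broader viruses are looked for depends on the earlier result and on the site's platform

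*Protocol article*

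**What the plan says.** Under Eligibility criteria, a participant qualifies through BioFire or through "other NHS Trust approved diagnostic PCR test during the current admission to be enrolled in the virus positive arm". The same section says that local platforms differ: "A range of viral PCR platforms are employed by NHS Trusts in the UK which detect common respiratory viral pathogens including RSV, influenza and SARS-CoV-2".

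The study's own BioFire run is then described for one situation: "If on admission, a potential participant has tested negative using a limited respiratory virus PCR panel". That run covers influenza, RSV and SARS-CoV-2 again and adds "parainfluenza viruses 1–4, human metapneumovirus, rhinovirus/enterovirus, adenovirus and coronaviruses 229E, NL63, OC43, HKU1". No section that is shown orders an extended panel for a participant who is already positive on a limited one.

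The Exposure section accepts BioFire or a site's validated PCR as alternative definitions of a confirmed infection. The Virus-negative comparison cohort section, by contrast, describes the main study group as positive by BioFire.

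Primary outcomes include "documenting the occurrence of various respiratory viruses, including influenza, RSV and SARS-CoV-2, but also a broader range of viruses", together with the association of these viruses with severity, progression and recovery. Subgroup analyses by virus are planned, and stratification by virus if numbers allow. For precision, the Sample size calculation says "1000/2000 participants would conservatively allow the estimation with a 95% CI of ±3.1%/2.2" percent.

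**The concern.** For patients tested first on a limited panel, a virus outside that panel is sought only if the panel's own targets were negative. Whether a virus was looked for therefore depends on which other virus had been found and on the platform the site uses. Three things follow for the primary outcome:

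- Broader-spectrum viruses are under-counted, because those accompanying influenza, RSV or SARS-CoV-2 in these patients go unrecorded.
- Comparisons between viruses are not like for like. The three common-virus groups contain unrecorded mixed infections, while the rhinovirus, parainfluenza and similar groups have mostly been screened for those three.
- Differences in virus mix between sites partly reflect the test used. The recruitment table shows centres opening and closing at different times, so platform, site and season can be entangled.

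The Bias section does not mention differential testing, and the covariates listed under Statistical methods include neither site nor platform.

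**Working it through.** **1. The plan's own figure.** The conservative 95% half-width for a proportion is 1.96 × √(0.25/n).
- n = 1000: 1.96 × √0.00025 = 3.10%.
- n = 2000: 1.96 × √0.000125 = 2.19%.

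Both agree with the stated ±3.1% and ±2.2%. They describe sampling error only, and a virus that was not tested for lies outside them.

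**2. Direction of the bias.** Two routes into the virus-positive arm can be set side by side:
- *Extended panel used first:* every listed virus is sought in every patient, and co-detections are recorded.
- *Limited panel first:* if positive, the patient qualifies and no further panel is prescribed. If negative, BioFire is run and all listed viruses are sought.

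On the second route, a virus outside the limited panel can be missed among limited-panel positives but cannot be over-counted. The error in the number of participants carrying such a virus is therefore downward, whatever the figures.

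**3. Illustrative size.** Missed share of the cohort = L × c × f. All three inputs are assumptions, since the documents give none of them:
- L, share of the cohort positive for influenza, RSV or SARS-CoV-2: 0.4 to 0.7.
- c, share of those who also carry at least one virus found only on the extended panel: 0.02 to 0.15.
- f, share tested first on a limited panel: 0.25 to 1.

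| Case | L | c | f | Missed share (points) | Per 1000 |
|---|---|---|---|---|---|
| Low | 0.4 | 0.02 | 0.25 | 0.2 | 2 |
| Middle, half tested limited-first | 0.5 | 0.10 | 0.5 | 2.5 | 25 |
| Near the stated half-width | 0.6 | 0.05 | 1 | 3.0 | 30 |
| Middle, all tested limited-first | 0.5 | 0.10 | 1 | 5.0 | 50 |
| High | 0.7 | 0.15 | 1 | 10.5 | 105 |

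The range runs from well below to above 3.1 points. It refers to carrying any such virus; for one named virus the shortfall is no larger. Given L, c and f, the missed share does not shrink as recruitment grows. If every positive participant had the extended panel, it would be zero.

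**4. Between-virus comparison.** The documents give nothing from which the effect on estimates of severity or length of stay could be sized. This part of the point rests on how the groups are formed.

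**The case against.** The strongest reply is that the rule sits in the eligibility section. It is there to find infections in patients who would otherwise be classed as virus negative, and it does not say that positives get no more virology. Swabs are taken from all participants ("The biological samples provided include blood, upper respiratory tract swabs and nasal lining fluid"), viral load is listed among the markers of interest, one section describes the positive group as positive by BioFire, and the pathway figure and sampling schedule are not shown. This stands to the extent that a reader who infers that limited-panel positives are never tested further goes beyond the text. What can be said is that the only stated rule leaves them out, and that the article is inconsistent about who has BioFire results.

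Three further inferences are tempting but not supported:
- *Mixed infections are invisible and the other virus groups are free of the common three.* BioFire re-tests for influenza, RSV and SARS-CoV-2, so a virus missed by the first test can still be found beside rhinovirus. Co-detection is reduced, not necessarily absent.
- *Untested viruses are recorded as not detected.* No section says how they are coded. That may be settled in the case report form or the statistical analysis plan.
- *The bias exceeds the stated precision.* It does so only under some assumptions; 600 × 5% = 30 per 1000, or 3.0 points, is already just below 3.1.

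Co-infection is also not a named outcome; it matters through virus occurrence and the make-up of the virus groups. The statement that the flow brings a broad range of pathogens into the study is not false, since it makes no claim of complete ascertainment in each person.

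It could also be said that denominators and coding belong in the analysis plan. That is fair for the coding. The testing rule, however, is a data-collection rule that this article states, and analysis cannot recover a test that was not run.

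**Conclusion.** The concern holds in this form: followed as written, the testing rule makes ascertainment of the extended-panel viruses depend on the earlier result and the site platform, which biases part of the primary outcome downward and makes the virus groups unlike one another. The direction follows from the text. The size does not: 0.2 to 10.5 percentage points rests wholly on the assumed L, c and f, and the gap does not arise where the extended panel is a site's first test. Because the size is unknown, the rule for positives is inferred from the only trigger given, and respiratory swabs are banked, this is a should-fix rather than a must-fix.

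**What to change.** 1. Reconcile the Virus-negative comparison cohort section (positives identified by BioFire) with Eligibility criteria and Exposure (BioFire or another PCR), and state which panel a limited-panel positive receives.
2. Unless all positives receive the extended panel, record the panel run for each participant and code each virus as detected, tested and not detected, or not tested.
3. Estimate occurrence of extended-panel viruses, and co-detection, only where the extended panel was run regardless of an earlier result, for example at sites or in periods using it first. Having a BioFire result is not a sufficient criterion, because that set includes patients selected for a negative limited panel.
4. Make the between-virus comparison under one stated rule: either that same subset, or a hierarchy that assigns any influenza, RSV or SARS-CoV-2 first and other viruses only if these three are negative. The hierarchy gives the same grouping on either route, provided the limited panel covers all three. Adjust for site or platform.

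The cost is wording, one recorded field and smaller denominators for these estimates, so the ±3.1% would no longer apply to them. Running the extended panel on stored swabs from limited-panel positives would close the gap more fully. It needs reagents and laboratory time, so it is an option and not a condition of the fix.
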